#### Sample size calculation

Studies on eHealth in CABG patients and the effect on healthcare utilisation are scarce and report users per resource [23]. Our primary objective is to reduce healthcare utilisation per patient. To our knowledge, in one study, healthcare utilisation per patient was estimated using the iMCQ at 0.88 ± 0.15.[24] Under the assumption of a small or medium effect of our eHealth strategy (d = 0.35), an α of 0.05 and a power of 0.80, a total sample size of 260 patients is required. The total study population is set at 280 patients (140 patients per arm) to account for loss to follow-up and nonadherence to the intervention.

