### Recruitment and allocation

All patients planned for preoperative outpatient counselling for CABG will be contacted by telephone in the week of their scheduled appointment. Patient eligibility for the trial will be assessed according to prespecified inclusion criteria (Tab. 1). Eligible patients will be informed about the study protocol by one of the investigators after their scheduled appointment. If the patient is willing to participate, the informed consent form is signed. At inclusion, patients are randomised to either the intervention or control group in a ratio 1:1 using block randomisation, with a block size of four.

**Table 1 Tab1:** Eligibility criteria

Criterium	
1	>18 years of age planned for elective, isolated CABG/OPCAB
2	Sufficient computer knowledge, and internet access. Children can assist, but patients should be able to access their own email and navigate the internet to use the provided eHealth strategy
3	Access to computer with internet connection and webcam or build-in camera
4	Comply to minimal specifications for use of video consultation:
	– PC/laptop: Windows 7 or 10 with Chrome or Firefox browser
	– Android tablet: at least Nougat software installed and use of Chrome browser
	– Apple iPad: at least iOS 12.3.4
5	Ability to speak, read and interpret the Dutch language
6	Provide informed consent

*CABG/OPCAB* coronary artery bypass grafting/off-pump coronary bypass

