### Statistical considerations

#### Data analysis

Descriptive statistics will be used to summarise baseline characteristics of the study population. Healthcare utilisation will be expressed as mean ± standard deviation (resource use per patient) and absolute and relative frequencies (users per resource). Mann-Whitney U test and Fisher exact test will be used to compare the intervention and control group. Multivariate regression analysis will be performed to adjust the outcomes for confounding factors based on univariate analysis (*p* < 0.1), literature review and expert opinion.

The primary analysis will be an intention-to-treat analysis. In the secondary analysis, we will compare the control group with the intervention group that used the educational videos at least once and completed the video consultations (‘users only’). A *p*-value <0.05 will be considered statistically significant and all analyses will be performed using SPSS 25 (SPSS Inc., Chicago, IL, USA).

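### 280 patients do not allow for nonadherence under the intention-to-treat primary analysis, and 0.88 ± 0.15 cannot be the mean and SD of a per-patient count

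*Protocol article*

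**What the plan says.** The Sample size calculation section of the protocol article cites one study in which "healthcare utilisation per patient was estimated using the iMCQ at 0.88 ± 0.15". It does not label the ± term. It then sets the effect directly on the standardised scale, "Under the assumption of a small or medium effect of our eHealth strategy (d = 0.35", and with "an α of 0.05 and a power of 0.80, a total sample size of 260 patients is required". The increase to the final number is explained in one sentence: "The total study population is set at 280 patients (140 patients per arm) to account for loss to follow-up and nonadherence to the intervention". Neither a loss rate nor a nonadherence rate is given, and d = 0.35 is never converted into contacts per patient.

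The Data analysis section says "The primary analysis will be an intention-to-treat analysis" and "Mann-Whitney U test and Fisher exact test will be used to compare the intervention and control group". The Primary outcome measure section describes a per-patient volume built from numbers of visits, so each patient's value is a whole number. Allocation is 1:1.

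**The concern.** There are two separate problems.

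- **The allowance.** Adding patients replaces those with no outcome data. It does not restore an effect that is diluted because some patients in the intervention arm did not use the intervention but are still analysed there. The stated reason for 280 therefore conflicts with the stated primary analysis. If nonadherence is appreciable, a trial described as having 80% power has less, and a null result would be given more weight than it deserves.
- **The planning figure.** The Data analysis section uses ± for a standard deviation, so a reader will take 0.15 as an SD. On that reading d = 0.35 looks like a very small change in contacts. A whole-number count with mean 0.88 cannot have so small an SD, so the reader cannot tell how large a reduction the trial is built to detect.

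**Working it through.** **Inputs.** From Sample size calculation: d = 0.35, α = 0.05, power 0.80, totals 260 and 280, planning value 0.88 ± 0.15. From Recruitment and allocation: 1:1. From Data analysis: intention-to-treat, Mann-Whitney. Assumed here: two-sided test, nonadherence q of 0 to 20%, no benefit in nonadherers, and d = 0.35 as the effect under full adherence.

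**Step 1: reproduce the 260.** Normal approximation: n per arm = 2(1.960 + 0.842)²/0.35² = 128.1, so 129. The exact two-sided t test gives 129.1, so 130 per arm, 260 in total, power 0.803. A one-sided test gives about 102 per arm and does not match. The 260 is a two-sided t-test size and is right.

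**Step 2: what the extra 20 buy.** 20/280 = 7.1%. A loss of 7.1% uses them all.

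**Step 3: intention-to-treat power with nonadherence.** The mean difference shrinks to d(1 − q). Two-sided t test:

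| Nonadherence q | Diluted d | 140 per arm (no loss) | 130 per arm (7.1% lost) |
|---|---|---|---|
| 0% | 0.350 | 0.83 | 0.80 |
| 5% | 0.3325 | 0.79 | 0.76 |
| 10% | 0.315 | 0.75 | 0.72 |
| 20% | 0.280 | 0.65 | 0.61 |

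With 140 per arm, 80% power needs d = 0.336, and 1 − 0.336/0.35 = 4.0%. So 280 tolerates about 4% nonadherence with no loss, and practically none if 7.1% is lost. For scale, 80% power would take 286, 320 or 404 patients in total at 5, 10 or 20% nonadherence before any loss, because the requirement grows as 1/(1 − q)².

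**Step 4: the planned test.** On normal data Mann-Whitney has relative efficiency 0.955: 129.1/0.955 = 135.2, so 136 per arm, 272 in total. For counts with control mean 0.88 and the difference set to d = 0.35 (pooled SD), simulated Mann-Whitney power with full adherence is:

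| Count variance (mean m) | 130 per arm | 140 per arm |
|---|---|---|
| Poisson, m | 0.76–0.77 | 0.78–0.80 |
| Overdispersed, m + m² | 0.72–0.73 | 0.76–0.77 |
| Overdispersed, m + 2m² | 0.71–0.72 | 0.74–0.75 |

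Each range spans two sets of runs (2,000 and 10,000 trials).

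**Step 5: the ±0.15.** For a given mean between 0 and 1, a whole-number count varies least when it takes only the values 0 and 1. The variance is then 0.88 × 0.12 = 0.1056 and the SD 0.325, more than twice 0.15.

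**Step 6: what d = 0.35 means.** Reduction in contacts = 0.35 × SD; relative reduction = that divided by 0.88.

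| SD | Contacts | Relative reduction |
|---|---|---|
| 0.15 (as printed) | 0.05 | 6% |
| 0.325 (minimum possible) | 0.11 | 13% |
| 0.94 (Poisson) | 0.33 | 37% (34% with pooled SD) |
| 1.29 (m + m²) | 0.45 | 51% (44% with pooled SD) |
| 1.56 (m + 2m²) | 0.55 | 62% (51% with pooled SD) |

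The contacts column and the first percentage use the control-arm SD. The pooled figures use the average of the two arms' variances.

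**The case against.** - **The sample size is not miscalculated.** This stands. The 260 reproduces, and 0.15 plays no part in it because d was assumed directly. Correcting 0.15 leaves 260 unchanged.
- **The dilution figures rest on assumed rates and on no benefit in nonadherers.** This stands as a caveat. The users-only definition requires both video use and completed consultations, so some non-users are partly treated and would dilute less. It does not rescue the claim, since about 4% full nonadherence is enough to reach 80% even with no loss.
- **d = 0.35 might already be the diluted effect.** Then no allowance for nonadherence would be needed, yet the text makes one.
- **The extra patients do help the secondary users-only comparison.** True: 140 controls against 120 users gives power 0.80 at d = 0.35 with no loss. But that is not the primary analysis.
- **The abstract says at least 280.** That makes 280 a floor, but the stated justification is still for 280.
- **The cited study's value may not be a plain count, or its ± may not be an SD.** Possible, since the source is not at hand. A reader might infer that 0.15 is a standard error; the documents do not say so.
- **A reader might infer that the trial can detect only a reduction of a third or more.** The documents do not support that. It needs roughly Poisson variance or wider and a control mean of 0.88, which is another study's estimate. Under Poisson variance the figure is about 0.35/√mean (control SD): 25% at a mean of 2 and 17.5% at 4. At mean 0.88 the printed figures force only 13%.
- **Mann-Whitney is a valid test for skewed counts.** Agreed. Simulated type I error was 0.046–0.053. Its low power for a 30% reduction (0.65 under Poisson) is mostly because that effect is smaller, about d = 0.31, and so is not evidence against the stated power.

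**Conclusion.** The point holds in two limited parts.

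First, the statement that 280 accounts for both loss and nonadherence is wrong for the intention-to-treat primary analysis. On the t test, at 10–20% nonadherence power is 0.75–0.65 with no loss and 0.72–0.61 after 7.1% loss, assuming no benefit in nonadherers. The planned Mann-Whitney test takes a further few points for counts: with full adherence and 130 per arm, power at d = 0.35 is about 0.76–0.77 under Poisson variance and 0.71–0.73 under overdispersion.

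Second, 0.88 ± 0.15 cannot be the mean and SD of a whole-number per-patient count. It leaves the 260 intact but makes the target effect unreadable: 6% as printed, at least 13% at any possible SD, 34–37% under Poisson variance and about 44–62% if overdispersed. Everything beyond 13% is an assumption, and all these percentages take a control mean of 0.88.

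The validity of the primary test and its type I error are not affected.

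**What to change.** In the Sample size calculation section:

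1. Check the cited source, say what ±0.15 is, and replace it with a possible SD if it is not one.
2. State the target effect in contacts per patient and as a relative reduction, over a range of plausible SDs.
3. Give the assumed loss and nonadherence rates separately.
4. Remove the claim that 280 covers nonadherence for the intention-to-treat analysis. If the extra patients are meant to support the users-only comparison, say so.
5. Restate power at 280 for Mann-Whitney over a grid of loss and nonadherence.

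The cost is a change of wording, a short calculation and a less favourable stated power. No extra patients are needed. A rate ratio with confidence interval from a count model would be a useful supplement on the scale of contacts per patient, but it is optional and not a correction.

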## Expected results

The IMPROV-ED trial will be carried out to evaluate whether an eHealth initiative consisting of online education and video consultation can reduce healthcare utilisation by improving quality of life, decreasing anxiety and accelerating recovery within the first 6 weeks after discharge for CABG.

## Discussion

The IMPROV-ED trial is of clinical significance for several reasons. First, we will evaluate the influence of an eHealth strategy on healthcare utilisation, anxiety, quality of life and recovery. Positive results will yield a new postoperative protocol that will lead to better patient outcomes and reduced costs [25]. In addition, the process and patient satisfaction evaluation will show the readiness of CABG patients for structured eHealth initiatives and will evaluate the currently used content and mode of administration, given the broad applicability of eHealth in general and the multitude of devices available [26–28]. Second, the control arm of the trial will provide the first detailed insight into unplanned, transmural healthcare utilisation in the early postoperative period after CABG and will thereby show how to further improve post-CABG protocols, aside from eHealth, through multidisciplinary regional collaboration.

eHealth strategies in CABG patients have been successfully applied to guide secondary prevention [29], to improve recovery [30, 31], and to assess physical functioning and quality of life [32–34]. Although evidence on the effect of eHealth on healthcare utilisation in CABG patients is minimal, it is reasonable to expect a positive effect based on reduction of healthcare utilisation by eHealth strategies in other populations [8, 23, 35, 36]. According to post-CABG protocols, patients are expected to adopt new behaviours (e.g. relieve stress on the sternum, gradually increase in physical exercise, follow healthy diet) and to deal with the emotions and worries that go with cardiac surgery through self-management, and, thus, to take responsibility for their own recovery [6]. eHealth has shown to be a useful method for patients to enhance their self-management through better understanding of their disease, increased independence and improved acceptance to adhere to lifestyle advice [37]. The educational videos in our eHealth strategy facilitate self-management. By means of video consultation, the physician can guide and supervise the patient’s progress and maintain a good patient-physician relationship, which has been shown to enhance the patient’s self-management skills [37].

The message and content of the educational videos were designed in such a way that they provide health information for patients with low/inadequate health literacy (approximately 36.4% of the general population in the Netherlands [38]), without compromising health communication to patients with adequate health literacy. Meppelink et al. have assessed the features of health information (written vs spoken text vs animations vs illustrations) and concluded that spoken text combined with animation is the most effective way to communicate health information and that it suits both patients with low health literacy and those with adequate health literacy [39]. In addition, to prevent cognitive overload, it is advised to only offer information when it is applicable to the patient’s situation instead of presenting all the information at once, especially to not overburden low health literate patients [40]. We therefore decided to divide the information into the three main phases of CABG recovery (Fig. 2).

### Limitations

The addition of our eHealth strategy to the postoperative protocol might yield additional costs in comparison to standard care. We believe that these additional costs will be balanced by reduced healthcare utilisation and will therefore result in less total costs and better patient outcomes. Another potential limitation is that we will only include patients that have sufficient computer and digital literacy skills and have access to a computer or tablet, which might diminish generalisability of our study protocol. Moreover, as in most eHealth research, our trial is not fully blinded, which could lead to bias when patients report healthcare utilisation.
